#### Staff

All staff allocated to the short-term stay groups in our study will be included in the quantitative part. In order to promote program integrity and to avoid contamination, group workers who work at the FC groups will preferably not work in the UC groups, and vice versa. The JJIs agreed to ensure as much staff-stability in the teams as possible, and to make an effort to keep staff consistent per group.

In addition, we will interview the group workers from the first two FC groups for the qualitative part of our study, as well as all group workers from the two UC groups. In each JJI, we will interview group workers from one FC and from one UC group.

At certain milestones during the study, we will bring a cake to the team meeting as an incentive for group workers for their family-centered activities or research-related activities. Team leaders will also discuss these activities in evaluation meetings with the group workers. For group workers’ participation with the interviews, they will receive the same incentive as parents.

### Recruitment and Sample Size

Adolescents and parents are informed of the JJI’s research activities by a flyer in the information leaflets from the JJI. The flyer informs that the data will be used anonymously in research studies and that parents can address their questions concerning these activities to their child’s mentor (one of the group workers) or to the psychologist.

The JJIs in the Netherlands jointly apply ROM and standard screening and diagnostic procedures for detained adolescents and their parents. As our assessments will be embedded in these procedures, the quantitative part of our study will use data collected in the two participating JJIs by these means. Recruitment of adolescents and their parents in the quantitative part of our study will last 21 months, including the pilot stage of 7 months. Based on records from 2011, the year prior to the pilot stage, we estimate that in 21 months, 300 adolescents will be placed in the groups concerned. Taking into account the exclusion criteria, we expect to recruit 160 adolescents and parents for the present study. Based on previous research, this number suffices for establishing statistically significant differences on quantitative measures between the two conditions [9].

As for qualitative studies, 10 interviews are generally sufficient to achieve saturation (ie, the point where additional interviews do not yield new essential information regarding the research question) [32]. Once an eligible adolescent is placed in a short-term stay group (either FC or UC), he and his parents will be invited to participate in the qualitative part of the study. If they are willing to participate, an appointment will be made for the interview. We will interview 10 boys (5 aged < 16 years and 5 aged > 16 years) in each JJI (N=20). We will also interview 20 parents (10 in in each JJI, 10 fathers and 10 mothers, 10 with a detained child aged < 16 years, and 10 with a detained child aged > 16 years). Finally, we will interview 20 FC group workers and 20 UC group workers.

### Programs

#### Family-Oriented Activities in Usual Care

According to the Dutch guidelines for UC, the adolescent’s mentor calls the parents within the first 10 days of placement of the youth to agree on weekly moments of telephone contact and to invite them for a meeting in the group, including a tour of the institution and its intramural school. The adolescent’s psychologist is invited to join part of that meeting as well. After the first 10 days, the mentor discusses which goals the adolescent wants to achieve and asks parents to sign for agreement. After three weeks, the mentor informs parents about the treatment plan and provides them with the opportunity to give feedback. Parents are invited for a meeting to discuss the second treatment plan after 12 weeks. If family-evenings are organized and if adolescents receive diplomas, parents are invited. Finally, parents may possibly be involved in treatment interventions for their child and in family therapy. All this is UC as outlined on paper; however, in practice these family-centered activities are barely translated into daily routine [16].

#### Family-Centered Care

An important aspect of FC is the training, ongoing coaching, and yearly booster sessions that JJI staff receive in working with parents. This training enables staff to adhere to the FC program with its more comprehensive and more structured family-oriented activities. In FC, staff members actively motivate parents to visit their detained child frequently and to take an interest in their child’s progress. Staff members also encourage parents to visit their child’s group and to join group activities such as cooking, sports, and playing games. The first phase of a youth’s detention is considered important in FC as the existing crisis is seen as an opportunity to establish engagement and build alliance with parents. A lot of emphasis is placed on the meeting in the third week of a child’s detention. During this meeting, the psychologist first meets the parents alone to learn about the family. Later, the adolescent and his mentor join the meeting. Parents are also invited for a variety of other meetings with staff, other parents, and youths where particular themes of general interest are being highlighted. Further, staff members actively and urgently invite parents to attend and have a say in all the meetings where the goals and the progress of the treatment plan for their child are being discussed. FC staff members are constantly in touch with the parents and give them regular (at least once a week) feedback on how their child is doing. If desired, parents can sign up for family therapy together with their child. This therapy–multidimensional family therapy (MDFT) or functional family therapy (FFT)–may already start when the adolescent is detained and will then be continued on an outpatient basis upon discharge of the adolescent from the JJI.

### Procedure and Instruments of the Quantitative Part of the Study

#### Assessments

The baseline assessment for adolescents and parents will take place in the third week of detention. The second (exit) assessment will be held in the week of the adolescent’s departure from the short-term stay group. Although our assessments will be embedded in ROM and in the standard screening and diagnostic procedures of JJIs, we will assist in scheduling assessments and we will help to interpret the scores of family-oriented questionnaires so that they are usable in clinical practice. The assessments will be carried out by trained research assistants or by trained students enrolled in one of the social sciences Master’s program, under supervision of the first author. Figure 2 presents an overview of the measures used for adolescents and parents.

**Figure 2 figure2:**
[figure not shown]
Overview of the quantitative measures for adolescents and parents; (FES) Family Environment Scale, (ATMQ) Adolescent Treatment Motivation Questionnaire, (JJI) Juvenile Justice Institution, (PSQ) Parenting Stress Questionnaire.

#### Demographics

Demographic data on age, place of birth, and ethnic background will be retrieved from the individual JJI database and from the joint ROM-JJI database. Because these databases do not contain information on family background, housing, past treatment, school careers, and jobs, we will use a short questionnaire to gather these data.

#### Family Interactions

The Family Environment Scale [33] (FES, in Dutch: Gezins Klimaat Schaal, GKS [34]) will be administered to adolescents and parents. This questionnaire consists of the subscales Cohesion, Expressiveness, Conflict, Organization, Control, Moral Standards, and Social Orientation. Each subscale contains 11 items. Questions are answered with “yes” or “no”. The FES has two underlying dimensions, Family Relationship and System Maintenance. The FES has adequate psychometric properties [35]. For example, regarding the internal consistency, the Cronbach alphas for the total group of mothers, fathers, and children differ between .63 (Social Orientation) to .70 (Cohesion). The Cronbach alphas for the System Maintenance and the Family Relationship dimensions are .78 and .82 respectively. The Cronbach alphas for the subgroups are higher than .60 for all subscales, except for Social Orientation for children (alpha=.38) [36].

#### Parenting Stress

We will use the Parenting Stress Questionnaire (PSQ, in Dutch: Opvoedingsbelasting Vragenlijst, OBVL) [37] for assessing the level of parenting stress experienced by parents. The PSQ targets individual characteristics of parents in relation to parenting and to the quality of the parent-child interaction. The questionnaire consists of 34 items to be scored on a four-point scale. Its five subscales are Parent-child relationship problems, Parenting problems, Depressive mood, Parental role restriction, and Physical health problems. The PSQ is shown to be reliable and valid. The Cronbach alphas for the five subscales are .84, .83, .83, .79, and .78 respectively. The total scale was also found reliable (alpha=.90) [38].

#### Satisfaction

We devised a questionnaire based on the Satisfaction Scale [39] and the Client-test (C-test, in Dutch: C-toets [40]), which we will use to determine how satisfied the adolescents and parents are with the JJI. These two questionnaires are shown to be reliable and valid [39,41]. Regarding the Satisfaction Scale for parents, all subscales for the inpatient/residential treatment center population demonstrate good internal consistency, with Cronbach alphas ranging from .76 to .94. For children, all subscales for the inpatient/residential treatment center population show good internal consistency, with Cronbach alphas ranging from .78 to .91, except subscale Access and convenience (alpha=.63) [39]. Cronbach alphas for the four subscales of the parent versions of the Client-test demonstrate good internal consistency, ranging from .77 to .90. The total questionnaire is found to be reliable (alpha=.94). The children version only has a total scale, which is found to be reliable (alpha=.91) [41]. Our satisfaction questionnaire has two parts, part A and part B. Part A contains 14 items to be rated on a three-point scale. It includes items such as “The staff members are friendly”, “I feel that the staff members are interested in me”, “The staff members treat me with respect”, and “The staff members help me dealing with problems”. Part B contains one question, “All things considered, which grade would you give to the service provided by the JJI?”, to be rated on a scale of 1-10.

#### Treatment Motivation

We will apply the Adolescent Treatment Motivation Questionnaire (ATMQ) to measure treatment motivation for adolescents. The ATMQ consists of 11 items to be rated on a three-point scale, adding up to a total score. The construct validity and internal consistency reliability are adequate (alpha=.84) [42]. We added three questions with a three-point scale to the ATMQ about adolescents’ motivation to take part in family therapy during their stay in the short-term stay group and about motivation for continued individual and family therapy after leaving the JJI. We also added four motivation questions to the Satisfaction questionnaire for parents (eg, “I am willing to participate in family therapy during my son’s stay in the JJI”, “I feel that my son needs treatment after his stay in the JJI”).

#### Parents’ Involvement During Their Child’s Detention

To examine to which extent parents are involved with their sons, we will record the number of visits by parents and the purpose of each visit to the JJI. Group workers, team leaders, and psychologists will note when they have had contact via telephone with the parents.

#### Incidents in JJIs

We will gather data on problem behavior as shown by the adolescents from routine daily reports and from JJI database input. JJIs record incidents such as verbal fights, physical fights, quarrels, rule breaking behavior, and possession of contrabands.

#### Cannabis Use

We will gather data on cannabis use from the JJI database. Routinely, JJIs collect a urine sample from the adolescent to check for traces of cannabis use as soon as he is placed in a short-term stay group. Later on during the stay, JJIs regularly perform urine screens, both at scheduled times and at random.

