### Study Objectives and Research Questions

The overall aim of our study is to evaluate FC in the first two years after the first steps of its implementation in short-term stay groups in JJIs. The key question to be answered in the quantitative part in the second stage of the study is if FC has additional value compared to UC. We will test the following hypotheses comparing FC with UC during detention: (1) FC increases parents’ involvement with their detained child; (2) FC increases the motivation of the adolescent and his parents for accepting treatment and guidance by JJI staff and for taking part in family meetings; (3) FC adolescents show less problem behavior; (4) FC improves family interactions; (5) FC parents experience less parenting stress; (6) FC youth more often return to their families’ home upon discharge; (7) FC enhances adolescents’ and parents’ satisfaction with the JJI; (8) In FC groups, JJI staff members are more satisfied, feel more confident in their contact with parents, and more often incorporate the family perspective in their thinking.

Finally, we will study if parents who participate in family-centered activities, differ from parents who do not participate based on characteristics such as proximity to the JJI, age of their child, duration of his stay, and baseline outcomes in other demographics, family functioning, parenting stress, treatment motivation, and satisfaction.

The aim of the qualitative part of the study is to trace which factors influence parental involvement. We will interview adolescents, parents, and group workers from short-term stay groups based on the following research questions: (1) How do adolescents, parents, and group workers feel about the current involvement of parents in FC and UC? (2) What are the attitudes of FC and UC group workers towards working with parents? (3) What are the needs, wishes, and expectations of adolescents, parents, and group workers concerning FC?

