### Analyses

#### Quantitative Analyses

All statistical analyses will be performed using SPSS 23. In a future paper, we will provide a flowchart of participants in our study, including reasons for exclusion. Descriptive statistics will be presented as means and standard deviations for all continuous variables and subscales. Additionally, frequency distributions or qualitative descriptions of all categorical variables will be presented for each group. The groups will be defined as FC or UC. We will test if these groups differ on demographic factors. If these differences exist, we will use these factors as covariates in our analyses. If necessary, we will also include the JJI in which an adolescent is placed as a covariate. We will perform within-group pre-post comparisons, between-group comparisons (FC vs UC), and repeated measures analyses. The selection of a specific test will depend on which hypothesis is tested and on the characteristics of the corresponding data (eg, categorical, ordinal, or interval level and normally or non-normally distributed). Table 3 shows the planned analyses to test our hypotheses for comparing FC with UC in case of normally distributed data. For combining the within-group pre-post comparisons and the between-group comparisons in our analyses, we will use the repeated measures ANOVA. Because the normality of the distribution of the data cannot be determined beforehand, the final analyses will be selected after the data is gathered. In analyzing the hypotheses, two-tailed analyses will be performed and we will correct for multiple testing.

**Table 3 table3:** Planned analysis for between-group hypotheses.

Hypothesis	Data source	Analysis
FC increases parents’ involvement with their detained child	Registration logs visits	Unpaired *t* test
FC increases the motivation of the adolescents and parents for accepting treatment and guidance by JJI staff and for taking part in family meetings	ATMQ youth total score Motivation items youth	Unpaired *t* test Pearson’s Chi-square test
	Motivation items parents	Pearson’s Chi-square test
FC adolescents show less problem behavior	Incidents in JJI Cannabis database	Unpaired *t* test Unpaired *t* test
FC improves family interactions	FES	Unpaired *t* test
FC parents experience less parenting stress	PSQ	Pearson’s Chi-square test
FC youth more often return to their families’ home upon discharge	Registrations logs living situation after discharge	Pearson’s Chi-square test

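### Cannabis outcome for hypothesis 3: the urine screen at placement precedes FC and UC, yet it is neither kept out of the outcome nor used as a baseline

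*Protocol article*

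**What the plan says.** The Cannabis Use section of the protocol article names one source: "We will gather data on cannabis use from the JJI database". It then describes two kinds of screen. The institutions routinely "collect a urine sample from the adolescent to check for traces of cannabis use as soon as he is placed". After that, "Later on during the stay, JJIs regularly perform urine screens, both at scheduled times and at random". It gives no number of screens per boy, no summary measure and no time window for the outcome.

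The section on study objectives sets the period of interest: "We will test the following hypotheses comparing FC with UC during detention". Table 3, under Quantitative Analyses, lists two data sources for hypothesis 3, "Incidents in JJI Cannabis database", each with the same test, "Unpaired *t* test Unpaired *t* test".

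The covariate rule in the same section starts from demographics: "We will test if these groups differ on demographic factors". Factors that differ become covariates, and the institution is added if necessary. The placement screen is not mentioned. A general sentence provides repeated measures ANOVA for combining pre-post and between-group comparisons, without naming the outcomes it applies to. The Assessments section sets the study baseline in the third week of detention.

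**The concern.** A sample taken at placement cannot reflect either program, because the boy has not yet been exposed to one. It is a pre-exposure value held in the same database as the outcome values. The planned test has no baseline term, and the covariate rule would not bring one in.

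Two things are at stake. If the placement result is counted, prior use becomes part of a measure meant to show behavior during detention. If it is left out but not used for adjustment, the strongest available baseline for this outcome goes unused in a comparison without randomisation. Cannabis is one of only two data sources for hypothesis 3.

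**Working it through.** **Inputs from the article.** One screen at placement; later screens, number not given; unpaired t test; no randomisation; three FC groups and two UC groups (Setting); 160 expected participants. The article has no figure specific to cannabis to reproduce, and it gives no effect size or standard deviation behind the 160.

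**Assumptions.** All positivity rates; k = 1, 2 or 4 later screens per boy; 160 boys split 3:2, so 160 × 3/5 = 96 FC and 160 × 2/5 = 64 UC; two-sided 5% level without multiplicity correction.

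**Step 1: formulas.** Let D be the FC-UC difference in intake positivity and δ the difference in later positivity. With the placement screen counted:
- share of positive screens: difference = (D + kδ)/(k+1)
- count of positive screens: difference = D + kδ

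**Step 2: balanced intake (D = 0), true effect of 10 points.** Take 50% positive at intake in both groups, and later 20% (UC) against 10% (FC). For the share:
- k = 1: (50+20)/2 = 35 against (50+10)/2 = 30, difference 5.0
- k = 2: (50+40)/3 = 30.0 against (50+20)/3 = 23.3, difference 6.7
- k = 4: (50+80)/5 = 26.0 against (50+40)/5 = 18.0, difference 8.0

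For the count the difference is 0.10k positives per boy whether or not the placement screen is included. Balanced intake adds noise there but no shrinkage.

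**Step 3: intake difference, no program effect (δ = 0).**

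| D (points) | Share, k = 1 | k = 2 | k = 4 | Count, any k |
|---|---|---|---|---|
| 8 | 4.0 | 2.7 | 1.6 | 0.08 |
| 15 | 7.5 | 5.0 | 3.0 | 0.15 |
| 20 | 10.0 | 6.7 | 4.0 | 0.20 |

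If placement is unrelated to the boys' characteristics, the standard error of D at 50% positivity is √[0.25 × (1/96 + 1/64)] = 0.081, about 8 points. The first row is therefore about one standard error. A gap of 20 points would be about 2.5 standard errors, an extreme case.

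**Step 4: simulation of the unpaired t test on the share (3,000 runs per case).**

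| k | Power, balanced intake, 10-point effect: counted / excluded | Rejection, no effect, intake 60% FC v 45% UC: counted / excluded |
|---|---|---|
| 1 | 18% / 43% | 33% / 5.0% |
| 2 | 43% / 71% | 26% / 5.3% |
| 4 | 82% / 94% | 18% / 4.5% |

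With equal underlying intake rates and no effect, rejection with the placement screen counted was 4.2%, 5.1% and 5.4%. Chance imbalance alone therefore does not inflate the error rate; a systematic difference does. Later screens were drawn independently given intake status, which probably flatters the power at larger k.

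**Step 5: why adjust as well as exclude.** Suppose later positivity is 20 points higher in boys positive at intake. With D = 15, excluding the placement screen still leaves 0.20 × 15 = 3.0 points with no program effect. The simulated rejection rates were 6.3%, 9.5% and 12.2% for k = 1, 2 and 4. In that model, conditioning on the placement result removes the 3 points.

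**The case against.** A reader might infer that the plan scores the placement screen as outcome and that the FC-UC comparison is therefore biased. The article does not support that. It describes what the institutions routinely collect, distinguishes the placement screen from later ones, and limits the hypotheses to the detention period. Turning a routine database into an analysed variable is also a detail that an article may leave to a fuller document.

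The analysis section does plan pre-post comparisons and repeated measures ANOVA, and intake against later screens would fit that frame. Table 3 covers between-group tests for normally distributed data, with the final choice after data collection. It lists the Family Environment Scale with only an unpaired t test too, although baseline and exit assessments are planned. A bare t test there does not prove that a pre-measure is ignored.

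The bias scenario also has to face the Setting section, which says that placement follows free slots and does not depend on the boys' characteristics. Stays under 14 days are excluded and later screens are regular, so nothing shows that k = 1 is typical.

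All of this stands as a limit on the claim. It does not remove the point. The repeated measures sentence is not tied to cannabis, the stated baseline is in week three, and the final choice of test turns on the hypothesis and on data type and distribution, not on which screens count. The covariate rule the article does fix leaves the placement result out.

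**Conclusion.** The point holds as a gap in how the article fixes this endpoint, not as a demonstrated error. A pre-exposure value sits in the named outcome source, and the stated test and covariate rule neither exclude it nor use it.

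If it is counted, any intake difference enters the result: divided by k+1 for a share, in full for a count. Shrinkage of a true effect by k/(k+1) applies to a share of positives and not to a count. The document gives no positivity rates and no numbers of screens, so the actual size is unknown; every figure above illustrates assumed rates. If placement is as independent as the Setting section states, the main loss is precision, plus dilution for a share. Bias needs a systematic intake difference, which the non-randomised design does not rule out. The change is worth making because it costs almost nothing.

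**What to change.** State that the placement screen is the baseline for cannabis use. Define the outcome from screens after placement only. Compare FC with UC in a model suited to the chosen outcome type, with the placement result as a covariate, in place of the unadjusted t test. Report by group how many boys have no later screen.

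The cost is a sentence in the outcome definition and one covariate already collected. Boys without a later screen do not contribute to this endpoint. A sensitivity analysis that counts a positive only after a first negative screen is optional, and the point does not depend on it.
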